### Statistical analysis techniques

#### Methods and models of data analysis according to the type of variables

We will utilize a cognitive model to integrate various data obtained from the study. Cognitive models describe how different aspects or variables interact and contribute to the observed behavior in empirical studies. Various influences come into play during the decision-making process, resulting in specific behaviors. Cognitive models provide valuable insights into the interconnected cognitive processes that contribute to the observed behavioral outcomes [5]. In this study, we propose to develop the following model:

$$DO_{i}=\overset{N}{\underset{j=1}{\sum }}\overset{P}{\underset{i=1}{\sum }}\overset{T}{\underset{k}{\sum }}f_{i}(f_{j}(ET),f_{j}(NA),f_{j}(EC),f_{j}(FI),CIT_{k})+\varepsilon$$

Therefore, a set of models will be trained using experimental data to describe the outcomes of individual decisions (i.e. *DO_i_*). Each outcome will be modeled as a combination of the aggregate characteristics of the research groups participating in the study (i.e., N) and their interactions with different versions of CIT supporting the war game (i.e., T), using a set of math functions. i.e., P) to describe these interactions (i.e., P).

Fig 1 presents a schematic example illustrating the expected outcomes of this research agenda. The scenario depicted in this figure suggests that the advantages of CITs peak at different levels of automation, depending on the specific planning team contexts. For instance, a group that with a substantial amount of pre-existing information may derive maximum benefits from CITs with moderate automation, as the abundance of available data may be associated with higher cognitive abilities. Conversely, a group with limited access to data may benefit from higher levels of automation to compensate for the lack of existing information. However, if the tools become overly complex for this group, the advantages of automation may diminish.

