## Method

### Research question

What is the marginal impact (i.e., the difference between performance in the and control condition) of the components of the TICs on people’s cognition and performance in complex and uncertain decision-making environments?

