#### Alternate hypothesis

There is an effect of the CITs on the decisions made in complex and uncertain scenarios.

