### Fundamentals of study design

CITs and ambiguity are defined and controlled variables.

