### Rationale for stratification factors

The participants in this study will consist of undergraduate or graduate students, and professionals from Tecnológico de Monterrey. All participants will be recruited through their teachers using a script and subsequently contacted via email to schedule an appointment in the study environment. The study topics will not be disclosed in class, and there will be no rewards or penalties for participation. All participants must volunteer and provide informed consent approved by the ethics committee of Tecnológico de Monterrey in Mexico.

One hundred and twenty (undergraduate and graduate students) will be divided into four research groups (RG). Each RG will comprise 30 individuals, with equal representation of 15 men and 15 women from various disciplinary backgrounds. The assignment of participants to each research group will adhere to the following experimental criteria:

RG 1: No computational system or ambiguity

RG 2: Unambiguous computer system

RG 3: Computational system with ambiguity

RG 4: Ambiguity without a computer system

Participants in the research groups will be carried out randomly while considering factors such as age, educational level, and sex to reduce intergroup variability. Each subject will belong to only one group and will participate in a single experimental session to avoid maturation and memory effects.

Regarding cognitive abilities, these factors will be analyzed post hoc to identify cognitive patterns associated with using CITs within the studied sample. Stratification based on cognitive conditions will not be conducted a priori, as the literature reports contradictory results between these conditions and the use of CITs and integrative complexity [8,9].

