The CIT will be an expert system based on artificial intelligence (SSEE), utilizing previous knowledge from the literature and the response options of the stimulus situation. Artificial intelligence will simulate the knowledge of an expert to solve a specific problem effectively. The resulting CIT will be unanimously validated by three expert judges in the use of computational tools in decision-making.

Participants will be presented with the interface, and only two research groups (RGs) will be asked to use the CIT to study the situation. Participants will have time to explore the decision-making situation and be guided through various phases of the interface. The decisions made by the participants will be entered into the CIT, which will provide feedback on the results of their decisions.

The experimental procedures will be divided into three steps, following the Solomon group experimental design. According to McCambridge et al. [17], Solomon’s 4-group design involves randomly assigning participants to four possibilities: (a) an experimental group with evaluations, (b) an experimental group without evaluations, (c) a control group with no assessments, and (d) a control group with no assessments. This design enhances internal validity by controlling for the effects of the baseline estimate and the interactions between the intervention and the baseline assessments.

Given that the present study examines the use of CITs in situations of ambiguity, the Solomon group design is an appropriate measure to observe the interaction between these variables within a single experimental design. The following groups will be established for the sample:

RG 1: No computational system or ambiguity

RG 2: Unambiguous computer system

RG 3: Computer system with ambiguity

RG 4: Ambiguity without the computer system

The inclusion of participants in the research groups will be carried out randomly, considering stratification and pairing factors based on their age, educational level, and sex to reduce intergroup variability. Each participant will belong to only one group and will participate in a single experimental session to avoid maturation and memory effects.

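### The only model written down holds fixed gaze and EEG signals recorded while the CIT is in use, and has no explicit ambiguity term, so its CIT term is not the marginal effect asked for

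*Protocol article*

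**What the plan says.** The *Research question* section of the protocol article asks: "What is the marginal impact (i.e., the difference between performance in the and control condition) of the components of the TICs". The alternate hypothesis is that "There is an effect of the CITs on the decisions made in complex and uncertain scenarios". The target is therefore a contrast between having and not having the tool.

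*Fundamentals of study design* states that "CITs and ambiguity are defined and controlled variables". The four research groups (RG) of 30 cross the two factors. For example, "RG 3: Computational system with ambiguity" stands against "RG 4: Ambiguity without a computer system", and RG 1 and RG 2 form the matching pair without ambiguity. *Research methodology* justifies the four-group design by its ability to show how the two factors interact. It also says that groups are formed at random, "considering stratification and pairing factors based on their age, educational level, and sex to reduce intergroup variability".

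The section *Methods and models of data analysis according to the type of variables* gives one model for decision outcomes (DO). Its inputs are "f_{j}(ET),f_{j}(NA),f_{j}(EC),f_{j}(FI),CIT_{k": ET, NA, executive control (EC), fluid intelligence (FI) and the CIT version. The text adds that the research groups enter through their aggregate characteristics, indexed by j.

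Two other places bear on the point. The *Decision Outcomes* paragraph says that the decisions of the research groups will be compared. The *Discussion* says that the data will first be analysed separately and then integrated.

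**The concern.** Step 1 of the procedure places the CIT exposure and the ET and EEG recordings in the same session, after assignment to a group. ET and NA are thus post-assignment variables that the tool can alter. The article expects this: in its eye-tracking section it says that using the CIT puts perceptual and cognitive demands on participants, and it anticipates that gaze will differ between groups. A model that holds such signals fixed removes whatever part of the effect runs through them. A tool that helps mainly by redirecting attention could then be reported as having little or no effect on decisions.

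In addition, the factor whose interaction with the CIT motivates the design has no visible place in the model, so the CIT effect under ambiguity (RG 3 against RG 4) cannot be read from it.

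**Working it through.** **Inputs from the article.** Four groups of 30: 4 × 30 = 120, which reproduces the stated sample. The CIT is present in RG 2 and RG 3, and ambiguity in RG 3 and RG 4. ET and EEG are recorded after assignment, during the task. The article gives no effect size or SD, so every effect below is an assumption in SD units with residual SD 1. The article speaks of unspecified functions to be trained; a linear form is used here only as an illustration.

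**1. Conditioning on a task-time signal.** Let the total CIT effect be 0.50 and let a share s of it pass through a gaze/EEG index. With the index in the model, the CIT term estimates 0.50 × (1 − s). A simulation of the 2×2 layout (30 per cell, 4000 runs, ambiguity effect −0.8, no interaction) gave:

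| Share s | 0.50 × (1 − s) | CIT + index, simulated | CIT, ambiguity, CIT × ambiguity and index, simulated | CIT, ambiguity and CIT × ambiguity without index, simulated |
|---|---|---|---|---|
| 0% | 0.500 | 0.496 | 0.495 | 0.496 |
| 25% | 0.375 | 0.378 | 0.378 | 0.501 |
| 50% | 0.250 | 0.250 | 0.250 | 0.499 |
| 75% | 0.125 | 0.126 | 0.126 | 0.501 |
| 100% | 0.000 | 0.000 | 0.000 | 0.501 |

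Adding ambiguity while keeping the index does not repair the loss. Removing the index does.

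**2. A common cause of signal and decision.** Suppose the CIT has no effect on decisions, shifts the index by 1, and an unmeasured trait loads c on both index and outcome. The CIT term then estimates −c²/(1 + c²):
- c = 0.3: −0.09/1.09 = −0.08 (simulated −0.08)
- c = 0.5: −0.25/1.25 = −0.20 (simulated −0.20)
- c = 0.8: −0.64/1.64 = −0.39 (simulated −0.40)

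If one of the two loadings changes sign, so does the bias. Its direction is therefore unknown in advance.

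**3. Leaving out ambiguity alone.** The cells are balanced, so CIT and ambiguity are uncorrelated and the average CIT effect stays at 0.50. The cost is precision. With an ambiguity effect of −0.8, the residual variance rises from 1 to 1 + 0.8²/4 = 1.16. The SE rises from √(1/60 + 1/60) = 0.183 to 0.183 × √1.16 = 0.197 (simulated 0.182 and 0.196), about 8%. The split by ambiguity is also lost: with an interaction of 0.4, the effects are 0.5 + 0.2 = 0.7 under ambiguity and 0.5 − 0.2 = 0.3 without it, but only the mean of 0.50 is seen.

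**4. Reading index j as carrying ambiguity.** Four group indicators have rank 4. Adding a CIT column leaves the rank at 4, because CIT is the sum of the RG 2 and RG 3 indicators. A separate CIT term is then not identified. A contrast among the four group effects would still be estimable, but the article does not state one, and it would still be conditional on ET and NA.

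**5. A concrete sign of the problem.** In the list of eye-tracking parameters, time to first fixation is counted from the moment the CIT appears. As worded, it has no value in RG 1 and RG 4, the two groups without a CIT.

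**The case against.** The best reply is that the written model is an integration step in an exploratory study whose main objective is descriptive. The hypothesis may be served by the announced comparison of decisions between groups, with its contrast left to a fuller document. Much of this stands. A reader might infer that the article contains no route to the marginal effect, or that the null hypothesis goes untested. The *Decision Outcomes* paragraph and the *Discussion* do not support that reading: the design can answer the question and a group comparison is planned. What remains is that the comparison has no stated contrast and is not named as the main test, while the one model written out has a different target.

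Other stronger readings also fail:
- The article does not say that RG 2 is pooled with RG 3 or RG 1 with RG 4; ambiguity could enter through the group index.
- Omitting ambiguity does not bias the average CIT effect.
- The absence of psychophysiological measures (PM) and integrative complexity (IC) from the model inputs is not a fault. They too can be changed by the CIT, and the secondary objectives treat IC as something the CIT acts on.
- Adjustment for the allocation factors is a detail that an article may leave to the analysis plan.
- No single attenuation figure can be claimed, since it depends on an unknown mediated share and unknown trait loadings.

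**Conclusion.** The point holds in this limited form. The CIT term of the written model is at best an effect with gaze and neural activity held fixed. It equals the marginal effect only if nothing passes through those signals and no unmeasured trait drives both them and the decisions. The total effect could be recovered by modelling ET and NA given CIT and averaging over them, but the article states no such step.

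The mismatch follows from the timing of the recordings and needs no numerical assumption. Its size does: anything from no loss to complete loss of a 0.50 SD effect as the mediated share goes from 0% to 100%, with possible further bias in either direction. The ambiguity part is smaller: some precision, and sight of the interaction that the design was chosen to show. The exploratory label does not remove the mismatch between the question and the model.

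**What to change.** Name the between-group comparison of decisions as the main analysis and state it as DO ~ CIT + ambiguity + CIT × ambiguity + sex + educational level + age, with no ET, NA or PM terms. Code ambiguity as ±0.5 so that the CIT coefficient is the average effect. Report that effect with a 95% CI overall and within each ambiguity level. Fit the same model with ET, NA, PM and IC each as an outcome, restricting ET metrics to those defined in all four groups.

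Keep the written model, with its CIT versions and automation levels, as a secondary exploratory process (mediation) analysis, and say that its CIT term is conditional on task-time signals. The main contrast answers CIT against no CIT. It does not answer the questions about components or degrees of automation, which stay with the secondary model.

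The cost is wording, one extra regression and no new data. Of the 120 − 4 = 116 residual degrees of freedom, three or four go to the allocation factors. The article should also say that the within-level results will be imprecise. With residual SD 1 and before covariate adjustment, the SE is √(2/30) = 0.26 SD for the CIT effect at one ambiguity level and √(4/30) = 0.37 SD for the interaction.

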### Research methodology

The research team will design a decision-making stimulus situation based on standardized decision-making paradigms validated in the existing literature, such as Ellsberg’s paradox. The characteristics of this decision-making situation will include non-linear behavior, multi-criteria results, ambiguity, and uncertainty. The stimulus parameters and narrative will be designed through computational experimentation to identify viable and robust interventions to serve as a baseline for analysis.

The stimulus situation will always be defined by choice interfaces that do not threaten the participants and will not involve monetary resources or real economic gains. These interfaces will be developed based on previously standardized situations described in the available literature, with defined parameters of ambiguity and validated performance in computational interfaces, such as Ellsberg’s paradox.

The Ellsberg paradox is an experimental challenge where participants make decisions about a possible outcome based on the probability of an event occurring [14]. This paradox is frequently used in decision-making theory [15,16]and has modulations in terms of ambiguity (amount of information offered to the decision-maker) and uncertainty (random result).

The experimental task of the Ellsberg paradox involves making a series of bets (without involving economic resources, only predictions) on the random selection of a colored ball in a lottery. The balls are red, green, or blue, and participants receive information about the total number of balls in a container, which varies in each round. Three decision conditions are presented to the participants. In the first condition, complete information is provided for each betting option, allowing participants to estimate which ball is most likely to be chosen. In the second condition, ambiguity is introduced by combining the frequency information of two balls into a single category, making it impossible for participants to determine which ball is more frequent and thus has a higher probability of being chosen in the lottery. In the third condition, participants are provided with a decision support tool that presents information about the probability of selecting each ball, considering all possible container frequency combinations (see Appendix 1 for images of the interface).

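### The model explains individual decisions from the aggregate characteristics of four research groups, so the CIT effect cannot be separated from the other predictors and between-person variation is lost

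*Protocol article*

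**What the plan says.** All of this is in the protocol article.

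- **Outcome.** Under 'Methods and models of data analysis according to the type of variables', models will be trained "to describe the outcomes of individual decisions", written DO with subscript i.
- **Predictors.** The same paragraph continues: "Each outcome will be modeled as a combination of the aggregate characteristics of the research groups participating in the study (i.e., N". In the equation, ET, NA, EC and FI enter only through functions indexed by j, which runs from 1 to N. CIT is indexed by k, described as the version of the tool.
- **Indices and error.** No index or term stands for the participant, and there is one unindexed error. The index i labels the outcome on the left and is also summed from 1 to P on the right, where the text says P counts mathematical functions.
- **Groups.** 'Rationale for stratification factors' states: "One hundred and twenty (undergraduate and graduate students) will be divided into four research groups (RG". It adds: "Each RG will comprise 30 individuals, with equal representation of 15 men and 15 women". The groups cross computer system (yes or no) with ambiguity (yes or no), and each person belongs to one group only.
- **Task.** 'Research methodology' says: "The experimental task of the Ellsberg paradox involves making a series of bets". The number of rounds is not given.

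**The concern.** The measurements are taken on individuals, and the stated interest is individual too. The secondary objectives ask about the impact of CIT components on people's cognitive bandwidth and integrative complexity. The article also promises to look for cognitive patterns associated with CIT use in the sample. A model that replaces each person's values by a group aggregate cannot address this.

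Two things are at stake. First, four groups supply too few distinct predictor values to tell a CIT effect from a difference in group-average ET, NA, EC or FI. Second, participants are randomised with stratification and pairing, so group averages of traits such as EC and FI should differ only by chance. Aggregation removes the variation that carries the information and keeps mainly noise.

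**Working it through.** **Inputs from the article.** Four groups of 30; the stated total reproduces as 4 × 30 = 120. Two of the four groups use the CIT. The predictors are ET, NA, EC, FI and CIT.

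**Assumptions for the count.** The functions are unspecified, so I take a linear form with one number each for ET, NA, EC and FI. This is lenient, because the article lists several eye-tracking metrics and nine EEG sites. CIT use is taken as fixed by group, as in the group list.

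**Step 1: group-aggregate predictors.** A predictor that is constant within each group is a linear combination of the four group indicators. Any set of such predictors, intercept included, therefore has rank at most 4.

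- Main effects: 1 (intercept) + 1 (CIT) + 4 (ET, NA, EC, FI) = 6 columns.
- With CIT interactions: 6 + 4 = 10 columns.
- A numerical check on simulated data for 120 people in four groups gave rank 4 for both matrices.

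The shortfall is 6 − 4 = 2 or 10 − 4 = 6 coefficients. Extra participants or bets repeat the same four rows and cannot raise the rank. The design factors alone (intercept, CIT, ambiguity, CIT×ambiguity) already use all four dimensions, which leaves 4 − 4 = 0 for the other predictors.

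**Step 2: individual predictors.** With each person's own ET, NA, EC and FI, the same 10-column matrix has rank 10, leaving 120 − 10 = 110 residual degrees of freedom. Adding ambiguity and CIT×ambiguity gives 12 terms and 120 − 12 = 108. The obstacle is the aggregation, not the sample size.

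**Step 3: the index i.** Once the right side has been summed over i, it no longer depends on i. It therefore cannot describe an outcome that differs by i.

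**Step 4: if single bets are analysed.** With m bets per person and within-person correlation ρ, the design effect for a group contrast is 1 + (m − 1)ρ. A single independent error understates the standard error by the square root of that. Neither m nor ρ is in the article, so these values are assumptions:

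| m | ρ | Design effect | SE too small by a factor of |
|---|---|---|---|
| 5 | 0.05 | 1 + 4 × 0.05 = 1.20 | 1.10 |
| 10 | 0.30 | 1 + 9 × 0.30 = 3.70 | 1.92 |
| 30 | 0.50 | 1 + 29 × 0.50 = 15.5 | 3.94 |

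In the middle row, 120 × 10 = 1,200 bets carry the information of about 1,200 / 3.70 = 324 independent ones.

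**The case against.** The strongest reply is that the study is exploratory and the equation is only proposed for development. The Discussion says the data sets will first be analysed separately and integrated later, so this equation need not carry the test of the CIT hypothesis. The index j also sits on the functions, so the formula alone could mean group-specific functions of individual data. These points soften the consequence but do not remove the problem. The prose says the inputs are aggregate characteristics of the groups, no index identifies a person, and an unidentified model cannot describe effects in an exploratory study either. This is a stated unit of analysis, not a detail left for a later document.

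Four stronger readings are tempting but not supported:

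- **The model must be either inestimable or give wrong standard errors.** A participant-level reading is open, is estimable (Step 2), and avoids bet-level clustering if each person contributes one summary outcome.
- **There are only four observations and no residual degrees of freedom.** The outcome is the individual decision, so even with 120 outcomes of rank 4 there are 120 − 4 = 116 residual degrees of freedom. The defect is rank deficiency of the predictors.
- **The type I error is inflated by a definite amount.** The article names no test, alpha or confidence interval for this model, and gives neither the number of bets nor their correlation. An unindexed error in a condensed article does not declare bets independent.
- **Leaving age, educational level and sex out of the equation is an error.** Groups are formed "considering stratification and pairing factors based on their age, educational level, and sex to reduce intergroup variability", but covariate adjustment is commonly settled in an analysis plan. Omitting balanced factors is also conservative. If they explained 5% to 30% of the outcome variance (assumed), the standard error would be too large by about 3% (1/√0.95) to 20% (1/√0.70).

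**Conclusion.** The point holds as a contradiction in the unit of analysis. Individual outcomes are set against group-aggregate predictors, and four groups allow rank 4 against 6 terms, or 10 with the CIT interactions. The model as worded cannot separate CIT from ET, NA, EC and FI, and it discards the between-person variation of interest. The term count assumes a linear form with one number per predictor; richer functions would need more terms. It does not depend on the number of participants or bets. If the CIT version varied within a group, versions could be compared there, but CIT against no CIT would remain a between-group contrast. The intercept and four group means would still be 5 columns of rank at most 4.

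The clustering point is secondary and conditional. It applies only if single bets are analysed without a participant term, and its size is unknown from the article.

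**What to change.** 1. Define i, j and k, use each for one purpose, and add an index for the participant.
2. Replace the sum over group aggregates by a participant-level model (n = 120) with each person's own ET, NA, EC and FI. Include CIT, ambiguity, CIT×ambiguity and the CIT-by-predictor interactions.
3. State the outcome unit: either one summary DO per participant, or bet-level data with a participant random intercept.
4. Optionally, add age, educational level and sex as covariates.

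The cost is one rewritten equation and its paragraph. The protocol already plans to measure every variable needed on each participant, so no new data or change to the sample size is required.
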